**STUDY POPULATION AND SIZE**

**Providers:** After analyzing the data from the historical data pull, we will study all providers with the ability to order advanced imaging. The exact number will be determined after analyzing the data, but we expect it to be on the order of 5000 providers. We will exclude CDS data from those providers who opt out. The categories of providers who are authorized to order advanced imaging include MD, DO, physician assistant, and nurse practitioner. Email address lists of providers in these provider categories will be obtained from Aurora and its affiliates. The opt-out email will be sent to these email addresses. This email includes a paragraph that providers are advised to read to their patients, in order notify them of the study.

**Patients:** Visits from all patients who are seen by providers in the study will be included and their outcomes analyzed. CDS may result in better-informed providers such that they are more likely to follow the American College of Radiology guidelines. This includes deciding not to scan. As a result, it is necessary to study outcomes for all patient visits, exclusive of behavioral health and excluding minors (age less than 18 years).

**EXPERIMENTAL DESIGN AND METHODS**

We propose a prospective, randomized controlled trial to measure the impact of CDS. Providers will be randomized into two arms: a treatment group that will receive feedback from the CDS system and a control group that does not.

- Aurora will send MIT a list of providers (encrypted IDs).  This will be for all providers who ordered an exam over the past 2 years who did not opt out of the study.
- MIT will randomize and create an indicator for treatment/control

(=0 or 1)

- MIT will send the encrypted IDs and their treatment indicator to Aurora
- Aurora will attach the treatment indicator to actual provider IDs
- The actual provider IDs and treatment indicator will then be sent by Aurora to NDSC*
- The order-entry system sends the order details, including the provider ID, to NDSC.  NDSC will write a script to display the best practice alerts only to those provider IDs in the treatment group.

Aurora will create and maintain the actual ID - encrypted ID crosswalk.

This will not be provided to MIT or NDSC.

*NDSC is the national decision support company. They provide the ACR Select

software. The provider ID will be sent to NDSC as part of the implementation

of ACR Select – and is not a research piece.

The CDS consists of several (bundled) components:

1. **Require selection of indication.** In order to properly score as many scans as possible, the order-entry software has been configured to require ordering providers to select a discrete indication from an existing list. This has been and will continue to be required of all providers: both treatment and control.
2. **Optional textbox to clarify indication selection**. There is an *optional* free-text box below the indication that allows providers to provide relevant additional clinical information for radiologists. This is available to all providers: both treatment and control.

The remaining features will be turned on only for providers in the treatment group and for providers who have opted out of the study. The below specifics are a business decision and a starting point for this project, independent of the research, and as such, are subject to modification.

1. **Display CDS at provider sign-off .** The CDS displays as a pop-up screen which appears when providers attempt to sign off on a scan. [name] will work with informatics physician leaders to determine a firing logic which minimizes provider alert fatigue.
2. **Only show appropriateness score.** The decision support tool will only show the appropriateness score, not costs or radiation exposure levels – though costs and radiation exposure levels are options on the CDS software.
3. **Only display alternative scans with a score of 7-9.** Only alternative scans with scores greater than 6 will be displayed in the CDS window. Only the highest rated scan alternative(s) will appear as “suggested” alternatives, while other alternative scans rated 7-9 will appear in the CDS window in order of appropriateness (*i.e.* first is the highest rated scan, etc.). This is an attempt to make it easiest to order the “most appropriate” alternative scan.
4. **Default to cancel scans.** Any time the CDS pop-up appears, a checkbox to remove the selected scan will be checked by default. This default can be over-ridden by the ordering provider by de-selecting the checkbox.^[[1]](#footnote-1)^
5. **Provide relevant ACR documentation.** A link to ACR documentation relevant to the indication category will be provided in the pop-up window.

**Informed Consent**

We are requesting an alteration of informed consent and a waiver of documentation of informed consent for the provider. We are requesting a waiver of Informed consent for the patient.

The following sections describe the justification that this research meets the definition of “minimal risk” as defined in the Common Rule.

**Minimal Risk Justification**

**Definition of Minimal risk:** “the probability and magnitude of harm or discomfort anticipated in the research are not greater in and of themselves than those ordinarily encountered in daily life or during the performance of routine physical or psychological examinations or tests”

**Provider + RCT + ACR Select**

Clinical decision support is commonly encountered in providers’ daily life on a national, regional, and local level. Providers experience ACR Select in daily life at about 80 institutions across the nation. Regionally, ACR Select either has been or is being implemented by most members of AboutHealth, the 8-member alliance of health systems in Wisconsin, of which Aurora is a founding member. Currently, providers in Aurora routinely encounter best practice alerts of many sorts in their normal use of the EMR (Epic). Absent this study, all of our providers would be seeing ACR Select decision support well ahead of the required date set by CMS.

The subjects may receive care that is more likely to follow the American College of Radiology guidelines. As the guidelines are considered best practice, we do not anticipate any adverse effect for these patients.

**Provider + RCT + No ACR Select Feedback**

This is current practice, and the risk of not using ACR Select is not greater than those ordinarily encountered in daily life.

**Patients of the providers (both with and without ACR Select)**

Insurers currently use a variant of appropriateness criteria for radiology benefit management, and the benefit or harm to patients is unproven and not measured. Aurora does not require preauthorization of patients for advanced imaging in the Aurora Accountable Care Network, which includes employees and others. So, we are currently applying CDS variably across our patient populations without any informed consent, and without understanding how this impacts patient care or costs. This current practice is not research, as we are not collecting/measuring data in a manner that constitutes to generalizable knowledge. However, this is something that patients encounter in daily life as a patient.

As a patient of a provider receiving ACR Select – a patient routinely sees providers who have different levels of technological access, and this is part of their everyday life as a patient.

The control group receives usual care as they are currently receiving it, therefore we do not anticipate any adverse effect of participating in the research for these patients.

**The waiver or alteration will not adversely affect the rights and welfare of the subjects**

**Providers as subjects:** The alteration of informed consent will not adversely affect the rights and welfare of the providers.

The decision to implement this clinical decision support rests with the organization, not with the individual provider. Although the providers now do not see the ACR Select decision support, they will see it ahead of the law’s requirement, regardless of whether or not this research is implemented.

Trial participation status will not impact employment, social status, or reimbursement to the employer.

Providers will be told about this study, and have the opportunity to opt out of having their CDS data analyzed. If they opt out, they will see the ACR Select decision support, as this will be the default for Aurora. Providers who opt out of the study prior to its start will not be randomized.

**Patients as subjects:** Patients’ rights and welfare will not be adversely affected by this waiver of informed consent. Their providers will continue to direct their advanced diagnostic imaging care based upon their training, experience, and ongoing review of the literature, upon which the appropriateness criteria are based.

**The research could not practicably be carried out without the waiver or alteration**

**Providers:** This research could not be practicably carried out without the alteration, which is very close to a waiver of Informed consent.

There is no practicable way to carry out this research without such an alteration. Anything less than almost full participation would skew the data. Opt-in programs typically have a low participation rate. For example, the simple difference between an opt-in (explicit consent) and an opt-out (presumed consent) process can push organ donation rates from, say, 4.25 per cent (in Denmark) to 99.98 per cent (in Austria). A low participation rate would severely limit the availability of data.

An e-mail notification that is brief, concise, and provides an opt out option and an opportunity to ask questions is a respectful, responsible way to inform the providers of this research, and have this research move forward. This research meets the definition of minimal risk, and does not adversely affect the rights and welfare of the subjects.

**Patients:** This research could not be practicably carried out without a waiver of Informed consent

There is no practicable way to carry out this research without a waiver. This study will be implemented at the provider level. This leads an informed consent process for patients to be impracticable for the following reasons:

1. We believe a part of the effect of the decision support may be from providers learning over time which types of scans are more or less appropriate in different clinical scenarios. It is impracticable for patients to decide not to be part of such a study because the providers are learning from their experience with other patients.
2. For this learning to occur as it would outside of a trial or research perspective, providers must have the opportunity to view the CDS alerts for each patient – not just a subset who consent. The characteristics of patients who consent to the study are likely to be systematically different from those who do not consent. This would bias the results of the research if consenters are more (or less) likely to have a condition for which a provider would order a more (or less) appropriate scan.
3. The consent process is likely to cause increased administrative burden, and impede or delay the normal course of care, as the patient reviews the consent form.
4. It is technologically infeasible to de-activate the decision support software for patients who do not consent.
5. All patients at Aurora see providers who could place an order, and consenting of all patients would be a monumental task and one that would result in the study not being performed.

Information on utilization and underlying health characteristics are essential for the measurement of the outcomes of this study: scan ordering patterns and downstream health utilization. Only de-identified information will be shared with MIT. This de-identified information will be coded, and Aurora will maintain the code (explained in Data Collection Section).

This research meets the definition of minimal risk and does not adversely affect patients’ rights and welfare.

**Whenever appropriate, the subjects will be provided with additional pertinent information after participation**

**Providers:** There will be no additional pertinent information to provide to providers after participation. The results may impact CMS decision regarding use/implementation. If a publication results, it will be available to providers throughout Aurora by means of ALIS.

**Patients:** There will be no pertinent information to provide to the patients as a result of the study.

**Waiver/Alteration of Informed Consent (45 CFR 46)**

This study meets the definition of Minimal Risk, and as such we are asking for an Alteration of Informed Consent and Waiver of documentation of informed consent for the provider. This alteration is in the form of an opt out email notification.

**Provider notification (Alteration of Informed Consent, opt out)**

The categories of providers who are authorized to order advanced imaging include MD, DO, physician assistant, and nurse practitioner. Email address lists of providers in these provider categories will be obtained from Aurora and its affiliates. The opt-out email will be sent to these email addresses. This email includes a paragraph that providers are advised to read to their patients, in order notify them of the study.

[name] and her staff will coordinate the notification of providers about the study. This will be in the form of an email provided as an addendum to this proposal. This coordination will entail responding to provider questions and keeping track of any provider who opts out of the study. Opting out of the study will mean that the data when that provider is the ordering provider will not be analyzed. Providers who opt out will receive the CDS tool, as it has already been adopted by Aurora and will be universally adopted in the near future. To clarify from the previous submission, these providers are not randomized—they are not part of the study.

The providers will be given several weeks to ask questions and / or opt out of the study.  It will take time for the research team to respond to questions and assemble the opt-out list.  Randomization will occur after the opt-out list has been assembled and given to Data Warehouse and Research Analytics.

**DATA COLLECTION**

The Data pull will be at the encounter-scan level. If there is no scan or one scan associated with an encounter, then there will be one record for that encounter. If there is more than one scan associated with an encounter, then there will be multiple records for that encounter (one for each scan). “Scan” means any study (including x-ray, ultrasound, CT, MR, PET, etc).

Patient and provider identifiers are needed at Aurora Health Care for the purpose of linking data elements across data sources. The data extraction process will be performed through each database separately in secured areas for patient data at Aurora Health Care.

The PI and team will combine these data and create a De-identified Data Set that will be shared with researchers from MIT. The data element list includes data from Epic, TSI, MSO, Strata, and NDSC. The data will include proxy unique identifiers for each patient and ordering provider to allow for tracking individuals over time. The Principal Investigator will be able to view the identifiable information and data warehousing and research analytics will maintain a crosswalk between the actual identifiers and the proxy unique identifiers. Data quality checks will be conducted by Aurora with help from MIT to ensure that the randomization takes place as planned.

This data pull does not affect clinical decisions.

**STATISTICAL PLAN**

The main analysis will compare outcomes for providers who were randomized to receive CDS compared to those who were randomized to the control group using regression analysis. MIT will perform the data analysis. They will compute Intent-to-Treat estimates as our primary method.

Consider an outcome, Y , such as the number of non-advised scans ordered by each provider provider. For provider i, the estimating equation is:

$$Y_{i}=\beta_{0}+\beta_{1}{1(\text{Treatment})}_{i}+\beta_{2}X_{i}+\varepsilon_{i}$$

where Treatment_i is an indicator variable equal to one if the visiting provider was randomized to the treatment group and zero if the provider was randomized to the control group; X_i is a vector of control variables. These control variables should be uncorrelated with the treatment indicator, but they can aid in the precision of the estimate. For our main specification, we will include only the lagged dependent variable (defined during the quiet period prior to study launch) since this generates a first order improvement in power to estimate an effect of the CDS. As robustness checks, we will examine these regressions without any controls as well as controlling for the full set of observable provider characteristics.

$\beta_{1}$ is the parameter of interest and measures the Intent to Treat (ITT): the causal effect of a provider being randomized into the treatment group.

Sometimes the provider who orders the scan is not the same as the provider the patient initially visits. One robustness check will use the treatment status of the visiting provider as an instrument for the treatment status of the provider who orders the scan in order to compute Local Average Treatment Effect (LATE) estimates.

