**SPONSOR**

MIT is the author of the protocol and the main grant awardee. Aurora Health Care is the potential sub-awardee of a grant from the Laura and John Arnold Foundation (LJAF).

**Version Date: July 13, 2016 (replaces** May 19, 2016)

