**CDS at Aurora**

Aurora Health Care implemented ACR select in October 2015. It is currently running “in the background” with no best-practice alerts being shown to providers. Best practice alerts will begin to be shown to providers in the near future in part because of new federal regulations. It is important to note that providers maintain their authority over imaging and treatment plans. The CDS intervention (Best Practice Alert) is non-obtrusive and can be easily overridden by the provider.

The Protecting Access to Medicare Act (PAMA) of 2014 [9] stipulates that provider-led entity developed CDS (such as ACR Select) must be consulted at the time of order entry for advanced diagnostic imaging performed on ambulatory Medicare patients. (Originally, the law specified January 1, 2017. The most recent regulatory commentary states that it will not be mandated by January 1, 2017 but does not specify when it will be mandated.) The law defines the ambulatory setting as inclusive of the provider office building or clinic, outpatient imaging performed in a hospital, the Emergency department, and the ambulatory surgery center. If proof of CDS consultation at order entry and a measure of how well the choice of imaging aligns with the appropriateness criteria are not attached to each Medicare claim, both the technical and professional reimbursement for the exam will be forfeit. Nearly all of Aurora Health Care's AboutHealth partners have implemented or are in the process of implementing CDS for advanced imaging across their systems, both inpatient and outpatient. To comply with the law and to stand with our partners in providing the most appropriate imaging care, Aurora Health Care has also done this.

While all providers are now entering a clinical indication for exam, the appropriateness is being scored in the background and stored without being shown to providers. This step, which is commonly taken by systems implementing CDS, allows measurement of baseline imaging utilization and appropriateness. We anticipate that when the mandate takes effect, the appropriateness scores and associated clinical decision support will be shown to all ordering providers at the point of order entry.

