**ENDOINTS**

Primary endpoints are:

- Ordering rate of scans of low utility (ACR score 1-3). This will be recorded as the number of inappropriate scans and the number of inappropriate scans per visit to the provider

- Provider diagnostic imaging rates: # of CT, # of MRI and # of total CT and MRI scans, as well as these measures per visit to the provider

Secondary endpoints are:

- Indication of change or cancellation of a scan

- Indicators of subsequent healthcare utilization/costs, such as:

• Subsequent scans

• ED visits

• Clinic visits

• Inpatient admission rate

• Number of inpatient admissions

• Procedures

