**Statistical Power**

Power simulations were conducted using two separate years of data for each provider (N=3506). We discovered that with this sample size and a 12-month study we would have the power to detect a 20% reduction in high-cost scans. This is similar to power calculations at another site, Mount Sinai Hospital in New York. Further, the rate of inappropriate scanning since the quiet period at Aurora began is on the order of 10%. At that rate, we will have the power to detect a 15% reduction in inappropriate scans, which is smaller than the effect sizes found in observational studies. In sum, we are powered to detect meaningful reductions in inappropriate scanning.

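### For the CT, MRI and total scan counts, the main model adjusts only for the quiet-period value; adding earlier ordering history as a second covariate could improve precision

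*Protocol*

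**What the plan says.** The protocol's Statistical Plan gives one regression for a generic outcome Y, with a treatment indicator and a covariate vector. For the main specification it states: "we will include only the lagged dependent variable (defined during the quiet period prior to study launch". The stated reason is precision: "since this generates a first order improvement in power to estimate an effect of the CDS". Two robustness checks vary the covariates. One uses none; the other is described as "controlling for the full set of observable provider characteristics", and its contents are not listed.

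The quiet period has a known start: "Aurora Health Care implemented ACR select in October 2015", and since then "the appropriateness is being scored in the background and stored without being shown to providers". The launch date, and so the end of the quiet period, is not given.

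The endpoints section lists two families of primary endpoint. One requires a score: "Ordering rate of scans of low utility (ACR score 1-3". The other consists of CT, MRI and total CT/MRI numbers, also expressed per visit, and requires none.

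The Statistical Power section shows that earlier data were available: "Power simulations were conducted using two separate years of data for each provider (N=3506".

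**The concern.** The quiet-period limit is forced for one family of primary endpoints and applied to both. A low-utility count cannot be formed before scoring began, but a CT or MRI count can. The only purpose the plan gives for the covariate is power, so for the scan counts it leaves out information that serves that purpose.

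High-cost scanning is also where precision is tighter. The protocol states a detectable reduction of 20% for high-cost scans against 15% for inappropriate scans, and its background section cites observational reductions in high-cost scanning of about 20%. The stated detectable effect therefore leaves no margin below the effect that earlier studies suggest.

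**Working it through.** **The plan's own figure.** The 20% detectable reduction cannot be reproduced. The protocol gives no alpha, power level, allocation ratio, mean, SD or baseline-outcome correlation, and does not say which baseline the simulations used. It can only be calibrated. Assuming 1:1 allocation (1753 per arm), two-sided alpha 0.05 and 80% power, 0.20 = (1.960 + 0.842) × CV × √(2/1753) gives a residual SD/mean ratio of about 2.11. Below, 20% is only a reference point, taken as if it applied to the quiet-period lag alone.

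**How much history lies outside the covariate.** The protocol carries "Version Date: July 13, 2016". From 1 October 2015 to that date is 286 days, about 9.4 months. The simulations had been run by then on two separate years of data, so at least 24 − 9.4 = 14.6 months precede the quiet period.

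**Stable-rate model.** Each provider has a constant underlying rate plus independent monthly variation. Let r be the correlation between two 12-month counts (assumed 0.6 to 0.9) and k = 12(1 − r)/r. A baseline of m months then explains R²(m) = 1/[(1 + k/12)(1 + k/m)], and residual variance is proportional to 1 − R². When rates are stable the best combination of two adjacent windows weights all months equally, so a quiet period of q months plus a separate 12-month covariate gives R²(q + 12).

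Example, r = 0.6: k = 8; R²(9) = 0.6/1.889 = 0.318; R²(21) = 0.6/1.381 = 0.434. Residual variance goes from 0.682 to 0.566, a 17% cut.

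| r | 9 months | 9 + 12 | cut | 12 months | 12 + 12 | cut |
|---|---|---|---|---|---|---|
| 0.6 | 0.682 | 0.566 | 17% | 0.640 | 0.550 | 14% |
| 0.7 | 0.555 | 0.438 | 21% | 0.510 | 0.424 | 17% |
| 0.8 | 0.400 | 0.300 | 25% | 0.360 | 0.289 | 20% |
| 0.9 | 0.216 | 0.154 | 29% | 0.190 | 0.147 | 22% |

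The detectable effect scales with the square root of residual variance. A reference value of 20% becomes 18.2% to 16.9% with a 9-month quiet period, and 18.5% to 17.6% with a 12-month one.

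**Decaying correlation, two 12-month windows.** Let ρ be the correlation between adjacent years and s that between the outcome year and the earlier year. Then R² = (ρ² + s² − 2ρ²s)/(1 − ρ²).

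- s halfway between ρ and ρ²: at ρ = 0.8, s = 0.72 and R² = (0.640 + 0.518 − 0.922)/0.360 = 0.658. Residual variance goes from 0.360 to 0.342, a 5% cut. Over ρ = 0.6 to 0.9 the cut is about 4-6%, so 20% becomes about 19.7% to 19.4%.
- s = ρ² (pure AR(1)): R² = ρ², and the gain is zero.

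**Separate covariate or one pooled mean.** A month-by-month drift model was run with a 9-month quiet period and 24 months of history in all, monthly autocorrelation 0.95 to 0.995 and 12-month correlation 0.5 to 0.9. Pooling everything into one longer mean moved the 20% reference to between 18.3% and 23.1%, so pooling can lose precision. Entering the earlier window as its own covariate gave 18.2% to 20.0%: a gain or no change.

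**The case against.** The strongest reply is that adjusting for one pre-randomization value of the same outcome is standard analysis of covariance, that the quiet period is the most recent window and matches the control condition, and that one rule for all outcomes limits specification choice. Covariate detail is also often left to an SAP. Most of this stands: the choice is defensible. But the protocol does not leave the covariate open. It fixes one and excludes others, and a second pre-specified covariate adds no analytic freedom.

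Several stronger readings are tempting, and the documents do not support them.

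- *The analysis is biased or invalid.* It is not. Treatment is randomized, and the ITT comparison holds with or without the extra covariate.
- *The baseline is nine months long and shorter than the 12-month follow-up.* The version date is not the launch date. Opt-out handling and randomization still had to follow, and the quiet period could reach 12 months or more.
- *All the needed history is in hand.* The power section shows it for 3506 providers, while about 5000 are expected. The two-year look-back in the design section yields a list of provider identifiers, not counts, and the historical data pull has no stated period or fields. Visit denominators from before the quiet period are not shown.
- *The gain should be measured from 9 to 24 months (19-32% on the same correlations).* Nine months plus the preceding 12 is 21 months, which gives 17-29%.
- *Earlier counts are fully comparable.* All providers must now select an indication. If that began with ACR Select, which the protocol does not date explicitly, earlier orders came through a somewhat different process. A separately estimated coefficient accommodates this; a pooled mean would not.

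The robustness check on provider characteristics might include earlier ordering. The text does not say so, and that check is not the main estimate.

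**Conclusion.** The point holds as an optional precision improvement for the CT, MRI and total CT/MRI counts, and it is minor. Nothing in the plan is wrong or contradictory here, and the ACR 1-3 endpoint is not affected. The benefit ranges from nothing (pure AR(1)) through about 4-6% of residual variance (partial decay) to 14-22% or 17-29% (stable rates, quiet period of 12 or 9 months). These figures rest on an assumed correlation of 0.6 to 0.9 and an assumed quiet-period length, neither of which is in the protocol. Confidence that earlier counts exist for the 3506 simulated providers is high. Confidence in the size of the gain is low.

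**What to change.** Add one sentence to the Statistical Plan before outcome data exist. For the CT, MRI and total CT/MRI count endpoints, the main specification will include two separate baseline covariates, the quiet-period value and the value for the 12 months before the quiet period, plus an indicator for providers without earlier data. Apply the same rule to the per-visit versions only where earlier visit denominators are available. Do not pool the two windows. Leave the model for low-utility scans as it is.

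The cost is one extra covariate and one indicator, negligible against some 3500 or more providers, and an extraction of earlier counts for providers outside the simulation set. The missing-history group may be larger than recent hires alone, so its size should be checked before launch. The correlation between the two years already analysed would show which part of the range above applies.
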